### What the Metabolic Health and Mother and Baby Health Outcomes Study Will Contribute

There are very few studies that use maternal characteristics to predict both maternal and fetal/neonatal pregnancy outcomes, even though they are inextricably linked. There are also few studies that consider the impact of metabolic disease as a whole rather than focusing on individual components of metabolic disease- hypertension, obesity, or dysglycemia.

We anticipate the Metabolic Health and Mother and Baby Health Outcomes (MAMBO) project will be able to fill this gap by developing a risk prediction tool that (1) considers how multiple maternal metabolic risk factors interact to result in adverse pregnancy outcomes, and (2) considers both maternal and neonatal pregnancy outcomes.

A risk calculator that can be used as a mobile app would provide health care workers with a simple effective tool to objectively calculate pregnancy risk and to triage women to appropriate services based on a standard dataset. Health care providers would require very little background knowledge to use the risk calculator. However, the tool would produce personalized data about the risks of an adverse pregnancy outcome. This would assist health care workers in effectively communication with the woman, her family, and with other health care providers.

### Limitations

Ideally, the MAMBO cohort would have been recruited prior to conception. However, this would have required a very large sample size to allow for women who did not conceive in a specified timeframe and for additional dropouts due to the lag time between recruitment and conception. Therefore, the pragmatic decision was made to recruit women at 20±4 weeks’ gestation. Existing data demonstrates a strong correlation between maternal anthropometric data and biomarkers in early pregnancy and the prepregnancy period [34].

The MAMBO cohort consists entirely of women attending major metropolitan maternity hospitals. Although these hospitals accept referrals from primary care and smaller hospitals that provide maternity care for women living in rural and remote locations, nonmetropolitan women are likely to be underrepresented in this cohort. Women from minority culture groups and women from non–English speaking backgrounds may also be less likely to participate in a prospective cohort study. To address these issues, translators and cultural liaison officers will be made available. We will aim to pair study visits with usual maternity care appointments. The final clinical study visit can be performed by phone if necessary.

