We hypothesize that the mothers and offspring at the highest risk of the adverse consequences of metabolic disease are predictable based on the phenotype of the mother prior to pregnancy. Despite the high fetal morbidity that can be associated with metabolic syndrome, little has been done to identify and capture at-risk individuals at a preconception or early antenatal stage. The aim of this study is to develop risk calculators that best predict (1) a mother’s risk of having a neonate with abnormal fetal growth (large for gestational age [LGA] or small for gestational age [SGA]); (2) a mother’s risk of having a serious adverse neonatal outcome; and (3) a mother’s risk of developing new metabolic disease after pregnancy (Figure 1). We will translate this to a user-friendly mobile app that will allow any health care worker to access and triage women to appropriate preconception care.

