### Recruitment Procedure

Women will be recruited when they attend maternity care visits between 16 and 24 weeks’ gestation. Initial contact will be made by the maternity care provider. Subsequent contact will be made by a dedicated study nurse/doctor at the time of the standard maternity care visit. All participants will receive standard individualized antenatal care based on their clinical needs.

No study activities will be performed before eligibility has been assessed and informed consent has been formally documented. To encourage attendance at clinical visits, parking and meal vouchers will be provided. At the final visit, women will be provided with a comprehensive summary of their metabolic health and a plan for appropriate long-term follow-up.

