#### Weight, Height, and Waist Circumference

Weight will be measured by a trained technician on calibrated digital scales with an accuracy of ±0.01 kg. Participants will be asked to wear light clothing but no shoes. Height will be measured by a trained technician using a standing stadiometer with an accuracy of ±0.5 cm. Waist circumference will be measured with an accuracy of ±0.5 cm using a standard tape measure according to the WHO guidelines (at the end of a normal expiration, at the midpoint between the lower margin of the last palpable rib and the top of the iliac crest, as the average of 2 measurements). BMI will be calculated by dividing weight in kg by height in meters squared.

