### Statistical Methods

This study will follow the Transparent Reporting of a Multivariable Prediction Model for Individual Prognosis or Diagnosis reporting guidelines for prognostic studies [14]. Summary characteristics of the study cohort will be described using means (with SD) or medians (with IQRs) for continuous variables, depending on the shape of the distribution, and numbers and percentages for categorical variables.

A risk calculator will be developed to determine the risk of an abnormally grown fetus (ie, the primary outcome of the study). Participant data will be split randomly into either training (70%) or validation (30%) datasets according to standard prediction model methods. Multivariable logistic regression analysis will be conducted to identify candidate predictors of poor pregnancy outcomes due to metabolic disease. After starting with the most comprehensive model that includes all potential risk factors for an LGA or SGA offspring (ie, the primary outcome). These include categorical variables including maternal SES (based on postcode), maternal parity, maternal smoking status, maternal obesity class, maternal preexisting diabetes, maternal preexisting renal disease, essential hypertension, use of antihypertensive medication, use of metformin, gestational hypertension, preeclampsia/eclampsia, previous LGA/SGA offspring, major congenital anomaly, and continuous variables including maternal age, maternal gestational weight gain, maternal glycemic control (HbA_1c_), total daily dose insulin, maternal systolic blood pressure, maternal diastolic blood pressure, birthweight of previous offspring, fasting glucose, plasma insulin, plasma C-peptide, plasma leptin, HOMA-IR.

A backward selection method will be performed to determine which combination of risk factors generates the most parsimonious predictive model. The number of candidate variables will be limited to data collected in the dataset. From this parsimonious model, model coefficients and the associated 95% CIs will be extracted to derive the risk score for predicting the delivery of LGA/SGA offspring. Internal validation of the model will be performed using 5-fold cross-validation and bootstrap validation. The performance of the model will be assessed using the AUC and calibration slope.

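### A calculator meant for preconception triage is to be derived from candidates that have no preconception value, or whose calibration for preconception inputs is not shown

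*Protocol article*

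**What the plan says.** **Use.** The Introduction hypothesises that the women and offspring at highest risk are "predictable based on the phenotype of the mother prior to pregnancy", and plans a "mobile app that will allow any health care worker to access and triage women to appropriate preconception care". Outcomes and Significance and the Conclusions repeat the preconception aim.

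**Measurement.** Under Recruitment Procedure, "Women will be recruited when they attend maternity care visits between 16 and 24 weeks". Table 1 places the first weight and blood tests at that visit.

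**Model.** Statistical Methods starts from a full list of candidates, applies backward selection, and takes the risk score from the fitted coefficients. The list includes gestational weight gain, gestational hypertension, preeclampsia/eclampsia and major congenital anomaly. It also includes HbA1c, systolic and diastolic pressure, and "fasting glucose, plasma insulin, plasma C-peptide, plasma leptin, HOMA-IR". The secondary outcomes are to be handled in a similar way.

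**Bridge.** Limitations says that recruitment before conception would have been ideal, explains why it was not feasible, and defends the timing with one sentence: "Existing data demonstrates a strong correlation between maternal anthropometric data and biomarkers in early pregnancy and the prepregnancy period".

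**Validation.** A 70/30 random split, 5-fold cross-validation and bootstrap, with AUC and calibration slope as performance measures.

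**The concern.** A risk score is valid for inputs that mean the same at use as they did at development. Here the coefficients and intercept come from values obtained during pregnancy, while the user is to enter values obtained before it. Two problems follow.

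- Some candidates do not exist before conception. If one is retained, the user has nothing to enter.
- Others exist at both times but may differ. A correlation says that women keep roughly the same order. It does not say that the values agree, and agreement is what predicted risks depend on. The cited correlation also concerns early pregnancy, whereas the study samples at 16–24 weeks.

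At stake are the probabilities that the app would show and the performance reported for it. An AUC helped by predictors that arise only in pregnancy would overstate what the tool can do before pregnancy.

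**Working it through.** The documents give no figure on this point to reproduce: no correlation size, mean shift or measure of agreement. The check has three parts.

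**1. Candidates against the moment of use** (my count of the list in Statistical Methods: 13 categorical + 12 continuous = 25)

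| Group | Candidates | n |
|---|---|---|
| No preconception value | gestational weight gain, gestational hypertension, preeclampsia/eclampsia, major congenital anomaly | 4 |
| Measured from Visit 1, may change in pregnancy | HbA1c, systolic and diastolic pressure, fasting glucose, insulin, C-peptide, leptin, HOMA-IR | 8 |
| Depends on the date to which the value refers | obesity class, smoking, antihypertensive use, metformin use, insulin dose | 5 |
| Essentially fixed | age, SES, parity, pre-existing diabetes, renal disease, essential hypertension, previous LGA/SGA, previous birthweight | 8 |

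4 + 8 + 5 + 8 = 25. I read major congenital anomaly as belonging to the current pregnancy. If an earlier child is meant, the first group falls to 3 and the point is unchanged.

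**2. What a correlation protects** (assumed values, illustration only)

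One standardised predictor has preconception value X0 and in-pregnancy value X1 = d + ρ·X0 + e, with SD 1 at both times. Here d is the mean shift in pregnancy and ρ the correlation. Development model: logit(p) = a + b·X1, with b = 1.35 and a set so that mean risk is 0.20. This gives a development AUC of 0.80, and the 20% and 0.8 match the assumptions under Sample Size. At use, X0 is entered in place of X1. Simulated results (500,000 women per setting):

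| ρ | AUC at use | Calibration slope | Mean predicted risk, d = 0 | d = 0.25 SD | d = 0.5 SD |
|---|---|---|---|---|---|
| 0.95 | 0.79 | 0.93 | 0.20 | 0.16 | 0.13 |
| 0.90 | 0.77 | 0.85 | 0.20 | 0.16 | 0.13 |
| 0.80 | 0.74 | 0.72 | 0.20 | 0.16 | 0.13 |
| 0.70 | 0.71 | 0.61 | 0.20 | 0.16 | 0.13 |

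Observed risk is 0.20 throughout. The AUC and slope depend on ρ. The error in mean risk depends on d and is the same at every ρ tried. A d of 0.5 SD moves every linear predictor by 1.35 × 0.5 = 0.675 on the logit scale. A shift in the other direction would make predicted risk too high instead.

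**3. Whether the planned validation could show this**

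The split, the cross-validation folds and the bootstrap samples all come from the same cohort and carry the same in-pregnancy inputs. They measure how well the model predicts from values collected in pregnancy. None of them enters a preconception value, so a good AUC and a slope near 1 there would say nothing about d or ρ.

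**The case against.** The strongest reply has five parts.

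- **The intended use is wider.** The Introduction also speaks of the need to "identify and capture at-risk individuals at a preconception or early antenatal stage". This stands as a fact, but the app is still described as triaging to preconception care. Nor does it rescue the list: total weight gain and hypertensive disease of pregnancy are not fully known at 16–24 weeks either.
- **These are candidates, not final terms.** Backward selection may drop the assays and leave mostly fixed predictors. This stands, and it makes the concern conditional. But nothing in the plan removes a predictor because it is unavailable before conception; selection follows contribution to the prediction alone.
- **The error may be small.** With correlation 0.95 and no shift the loss in the illustration is slight. A reader might infer that the coefficients do not apply before conception. The documents do not support that; they support only that applicability has not been shown.
- **Obesity class.** A reader might infer that it comes from weight at Visit 1, since "BMI will be calculated by dividing weight in kg by height in meters squared" follows a description of measured weight. Statistical Methods does not say which weight is used, and the maternal outcome definition refers to prepregnancy weight. No misclassification can be claimed.
- **Availability of the assays.** A reader might infer that users could not obtain insulin, C-peptide or leptin. The documents do not say so, and they describe HbA1c and glucose testing as part of clinical care.

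The timing is also openly disclosed, with a feasibility reason. The weakness is in the justification; nothing was concealed.

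**Conclusion.** The point holds in conditional form. The stated moment of use and the candidate list do not match: 4 of 25 candidates cannot be entered before conception, and 8 more are measured only from 16–24 weeks and may change in pregnancy. If any of the 4 is retained, the calculator cannot be run for its stated purpose. If any of the 8 is retained, its calibration for preconception inputs is not shown. The coefficients of the fixed predictors would then also be conditional on those terms. The correlation argument does not close the gap, and the planned internal validation cannot test it.

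The size cannot be taken from the documents. The illustration runs from almost no loss (correlation 0.95, no shift) to a mean predicted risk of 0.13 against 0.20 (0.5 SD shift). It rests on one predictor, equal SDs and assumed shifts, so it shows what kind of error is possible and does not forecast one.

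**What to change.** For each outcome, prespecify that the preconception calculator uses only predictors known before conception: age, parity, smoking, SES, obesity class from prepregnancy weight, pre-existing disease and its treatment, and obstetric history. Define smoking and treatment by their status before the pregnancy. Prepregnancy weight has no row in Table 1, but the Secondary Outcomes definition of new overweight/obesity already requires it; state its source. Base all preconception claims, and the AUC and calibration reported for the app, on this model.

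Optionally, report a second model that adds Visit 1 measurements, labelled for use at 16–24 weeks, with its gain in AUC over the first. Leave predictors known only later in pregnancy out of both.

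**Cost.** No new recruitment, and the Results section says that no analysis has been done. With three outcomes this means three preconception fits and validations, or 3 × 2 = 6 if the second model is added. The preconception model will probably show a lower AUC. The Discussion reports 0.63 (preterm birth/SGA) and 0.64 (LGA) for basic preconception models elsewhere, although these are not the composite used here. A lower figure would be the honest one for the intended user.

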### Outcomes and Significance

Growing numbers of women are impacted by metabolic disease when they pursue pregnancy. However, women of low socioeconomic status, non-English speaking backgrounds, and women living in rural and remote areas are less likely to access preconception care services. Therefore, these women are at a greater risk of short-term adverse pregnancy outcomes, and long-term due to metabolic programming in the infant and unmasking of endothelial dysfunction in mothers.

The development of a risk calculator that predicts the women most likely to have poor pregnancy outcomes may assist in preventing these adverse pregnancy outcomes. It would allow women to be triaged by any health care professional and would ensure that the highest risk women are identified and have the opportunity to be referred to high-quality preconception care services and to receive information on how to prevent adverse health outcomes for themselves and their offspring. The risk calculator also has the potential to act as a platform that assists health care professionals in providing lower-risk women with basic preconception care information.

### Conclusions

Currently, the women at the highest risk of adverse pregnancy outcomes due to metabolic disease are the least likely to access preconception health interventions. The MAMBO project intends to bridge this gap by developing a risk prediction tool that allows any health care practitioner to accurately assess risk, and to triage women to appropriate preconception care services. In this way, we aim to prevent adverse maternal and fetal health outcomes.

## Appendix

Multimedia Appendix 1 Additional tables.

## Abbreviations

AUC: area under the receiver operating characteristics curve
GDM: gestational diabetes
HbA_1c_: hemoglobin A_1c_
HOMA-IR: homeostasis model assessment of insulin resistance
IADPSG: International Association of the Diabetes and Pregnancy Study Group
LGA: large for gestational age
MAMBO: Metabolic Health and Mother and Baby Health Outcomes
OGTT: oral glucose tolerance test
REDCap: Research Electronic Data Capture
SGA: small for gestational age
T2D: type 2 diabetes
WHO: World Health Organization
